##### Intermediate transfer

To measure perceptual and psychomotor speed, digit symbol from Wechsler Adult Intelligent Scale fourth addition WAIS-IV [38] and Perdue pegboard [39] will be used. In Digit symbol the participants are given a paper with a number coding key with numbers 1–9 associated with different geometric symbols on top of the assessment sheet. Further down on the assessment sheet numbers are shown together with empty boxes and the participants are instructed to draw as many geometric symbols in the empty boxes associated with the different numbers for 2 min. The total number of correct symbol drawings will be used as an outcome measure. Perdue pegboard is a test of fine manual dexterity of the upper limbs [40]. A white board with two cups containing small metal rods and two vertical rows of small holes is placed in front of the participant. The participant is asked to take a pin, one at a time from the right/left or both cup/s, and place in the holes starting at the top of the board on the right/left or both vertical line/s and repeat this during 30 s. Each condition is repeated 3 times. The outcome measure is the mean number of rods completed for each condition (right (or dominant)/left (or non-dominant)/both). The mean number of completed rods for the side most affected by PD will also be used as an outcome measure.

Working memory will be tested with digit span -forward, −backward, −sequencing, and spatial placing. Digit span forward, backward, and sequencing will be administered according to WAIS-IV [38]. Digits are presented orally with a rate of 1 sec per digit. The participants are instructed to remember the digits and report them back in the same order (forward), in reversed order (backward) and sequential order from one to nine (sequential). Two trials are presented for each span level. If the participant fails to report the digits in the correct order in both of the trials at one level the test is terminated. Both the total score and the highest span level (forward, backward, and sequential) will be used as outcome measures. Total min-max for each list (0–16) Total min-max for all lists (0–48), Span level min-max (forward 2–9, backward 2–8, sequential 2–9). Spatial working memory will be tested with an in-house developed computerized task named the “square” [41]. The participant will be presented with a 4 × 4 grid of squares. A square is lit up in red in random serial order and the participant will be asked to remember and report the squares that are lit up by clicking on the squares in the correct order after the presentation. Three trials are presented each span level starting with two spatial locations. If the participant fails to report the spatial location in the correct order in two of three trials at one level the test is terminated. Both the total score and the highest span level will be used as outcome measures. Total min-max (0–27), span level [2–10].

Inhibition will be measured with the Stroop task [42], administered according to standard procedures from the Delis-Kaplan Executive Function System (D-KEFS) [43]. The first test condition consists of 50 colored squares (red, green, and blue) printed on a sheet of paper that the participants are asked to name aloud. The second condition is to read 50 color words (red, green, and blue) written in black ink. In the third condition, there are 50 color words (“red”, “green” and “blue”), in red, blue, and green ink not matching the written word. The participant is asked to name the ink color. The instruction for all the lists is to complete each list as fast as possible without making any mistakes. Time in seconds to complete a list will be used as outcome measures. To get an inhibition score the third list minus the mean of list one and two will be calculated.

Shifting ability will be measured by the Trail Making Test (TMT) from D-KEFS [43]. The participants will be presented with a paper containing circles with letters and numbers in two different subtests. In the first test (TMT part 2) the participant will be asked to draw lines between circles in numeric order. In the second subtest (TMT part 4) the participants will be asked to draw lines between circles alternating between numbers and letters in numeric and alphabetic order (1-A-2-B-3-C…). Time to complete each subtest will be used as outcome measures. A flexibility score will also be used as an outcome measure calculated by subtracting TMT part 2 from TMT part 4.

##### Far transfer

Episodic memory and learning will be measured by an in-house developed program of free recall of 18 nouns administered according to Buschkes’ selective reminding procedure [44]. Initially participants will be presented with a list of 18 words presented serially on a computer screen with a stimuli presentation time of 5000 ms per item. The presentation is followed by a free recall test. Words not recalled successfully are presented to the participant verbally by the test leader with a 5 s stimuli interval on three subsequent trials. After each presentation the participant will be asked to recall the complete list again. A delayed recall performed 20–30 min after the learning phase will also be conducted. Three different lists of words will be counterbalanced among participants and test occasions. Total numbers of correct recalled words (max = 72) total numbers of correct recalled words for the trial with the best performance (max = 18) and total numbers of correct recalled words in the delayed recall (max = 18) will be used as outcome measures.

Fluid reasoning (nonverbal intelligence) will be measured by Matrices from WAIS-IV [38]. One (1 × 6) or two (2 × 2) dimensional matrices are presented to the participant. One section is missing in each matrix and the participant is asked to choose between one of five- alternatives that fit in the missing section. The session is terminated after three wrong answers in a row. There is a total of 26 items. Before the test two training items are presented where feedback is given to the participant. The total number of correct answers will be used as outcome measures (min-max: 0–26).

#### Other pre-specified outcome measures

##### Questionnaires

Subjective cognitive complaints will be assessed with the Prospective retrospective memory questionnaire (PRMQ) [45], a 16 item long questionnaire of memory slips in everyday life equally divided between questions about prospective memory problems such as “Do you decide to do something in a few minutes and then forget to do it” and questions about retrospective memory problems such as “Do you fail to recognize a place you have visited before”. Answers are given on 1–5 points Likert scale where 1 = never and 5 = very often.

The Hospital Anxiety Depression (HAD) scale is a 14 item long questionnaire equally targeting anxiety and depression, answers are given on a 0–3 Likert scale where 0 = never/no problems and 3 = always/a lot of problems. To measure general health status the short-form health survey (SF-36) will be used [46]. The questionnaire consists of 36 questions. The answers given varies between yes and no answers and Likert scales with three to six alternatives. The scale can both be used as a total score for general health and divided into physical function, role limitations physical and role limitations emotional, energy/fatigue, emotional wellbeing, social functioning, and pain. To assess sleep the short form of the Karolinska Sleep Questionnaire (KSQ-short) [47] will be given to the participant, a self-assessment form that measures different aspects of sleeping difficulties the past month. The KSQ-short form consist of six questions were the answers are given on a five-point Likert scale from 1 = never/very good to 5 = always/very bad. The Parkinson’s disease Questionnaire (PD-39) assessing function and wellbeing related to PD will be given to the participants. It consists of 39 questions were the answers are given on a Likert scale from 0 = never to four = always (cannot do it at all). Fatigue is assessed with the Checklist Individual Strength (CIS) [48], a self-assessment form consisting of 20 items rated on a seven-point Likert scale from 1 = yes, that is true to 7 = no, that is not true. Higher scores indicate more symptoms/problems for all measures.

##### Risk-taking

Impulsivity and risk-taking are assessed with Urgency, Premeditation, Perseverance, and Sensation Seeking (UPPS) and The Balloon Analogue Risk Task. UPPS is a self-administered questionnaire consisting of 45 questions rated on a 4 point Likert scale from 1 = completely true to 4 = completely false. The questions are divided into four factors of impulsivity related constructs [49]. Risk-taking is assessed with an in-house developed computerized test based on the Balloon Analogue Risk-taking Task (BART) [50]. The participant is presented with a balloon on the screen, which can be inflated by air by pressing a digital button with the left mouse key. The participant is told that the larger the balloon gets the more points are gained. The assignment is to get as many points as possible. If the balloon explodes, no points will be gained for that balloon. The computer program displays the size of the balloon visually and there are air puffing sounds for every time the participant inflates the balloon. There is also a pop-sound every time a balloon explodes. Each balloon is programmed to pop between 1 and 128 pumps. Information regarding the balloon breakpoint is not provided to the participant, who is told that the balloon can break at any time from the 1st pump. The participant can at any time stop pumping the balloon and collect their points by pressing the collect button. The outcome variable is average number of pumps for all the balloons that did not explode.

#### Compliance and adherence

Completing training on schedule, with 4–5 training sessions a week will be used as a measure of compliance to the study protocol. To minimize the dropout rate there will be supervision through telephone contact and e-mail/SMS regularly during the training period (see Table 3 for contact schedule). The online program will automatically record and store the time, date, Self-assessed motivation, and ability to stay focused during training, as well as the results for each training session.

**Table 3 Tab3:** Adherence schedule with contact plan

Phone call	5–7 days
Mail or sms	2 weeks
Mail or sms	4 weeks
Mail or sms	6 weeks
Phone call	6–7 weeks

#### Potential moderating and mediating factors

Baseline factors such as age, gender, cognitive performance level, handedness, and education level will be collected at baseline. Information such as date of diagnosis, start of motor symptoms, Unified Parkinson’s Disease Rating Scale (UPDRS), Hoehn and Yahr stage, MMSE, disease laterality, starting symptom, laterality of symptoms at diagnosis and information regarding pathological DaTScan will be collected from the participants’ medical journal. Disease duration will be calculated as the time from date of diagnosis to pretest, while symptom duration will be calculated as the time from self-reported symptom onset to pretest.

#### Placebo effects due to expectations

The participants will be told that they are randomly allocated to either a memory-based intervention or an attention-based intervention. To reduce expectations in favor of one of the interventions both training programs are presented as equal alternatives. Both groups will get identical instructions on how the training program works and the research team does not speak in favorable terms for one intervention over the other. According to Boot et al. the effectiveness of the intervention could be questioned if the perceived intervention benefit correlates with improvement in that particular task [51]. To be able to measure expectations in relation to training gain, questions, whether the participant believes the intervention has led to an improvement in four different tests (Digit Symbol, Letter Memory, Matrices and n-back), will be assessed before each test during posttest (both directly after training and after 16 weeks).

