### Intervention

The training program is web-based and conducted at the participant’s home four to five times a week for a total of 30 training sessions. The total training period will vary between 6 to 8 weeks. Each training session will be unsupervised and takes 20 min to complete. The training program consists of one criterion task and three training tasks that all aim to train the working memory updating function. The tasks will be performed in the same order for each training session. Participants will be asked how motivated they feel before each training session and how they perceived their ability to stay focused during training after each session. All items have a presentation time of 2000 ms with a stimulus interval of 1000 ms and the time to answer is unlimited. Feedback concerning numbers of correct answers are provided after each item as well as after each training task. The updating training program is adaptive to the participants’ performance and consists of three difficulty levels for all tasks except the criterion training task. When the participant performs at 80% or better at one level, they will advance to the next level for that specific task.

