**Other Pre-specified outcome measures**					
Subjective cognitive complaints	Prospective retrospective memory questionnaire	X		X	X
Depression and anxiety	Hospital Anxiety Depression scale (HAD)	X		X	X
Health status	Short form health survey (sf-36)	X		X	X
Sleep	Short version Karolinska Sleep questionaire	X		X	X
Function and well being	Parkinson’s Disease Questionnaire PDQ-39	X		X	X
Fatigue	Checklist Individual Strength questionnaire (CIS)	X		X	X
Impulsivity and Risk taking	Urgency, Premediation, Perseverance and Sensationseeking (UPPS)	X		X	X
	Balloon analog test	X		X	X
Adherence (task engagement)	Self-assessed motivation and ability to stay focused during training		X		
Compliance	Number of participants finishing within time frame		X		
Expectation	Expectation of improvement in certain tasks			X	X
Self-assessed improvement and adverse events	Evaluation of the training			X	X

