This study has many strengths. Among them is the inclusion of an active control condition similar to the intervention of interest in all aspects except that the control condition does not include any updating in the training tasks. The majority of intervention studies use a no-contact or waiting list control and if a control-intervention is implemented it is often different from the training intervention, leading to a difference in expectations. To minimize the effect of expectation and to enable blinding, both study arms of the iPARK trial will be presented as equal interventions. Nevertheless, expectations of improvement will be measured before some post-tests to see if the two groups differ in that respect. Thereby, the iPARK trial will be able to answer if it is the updating itself that is causing the improvement. Furthermore, the iPARK trial will establish if there are any moderating factors for improved cognition after training in PD such as baseline cognitive function, age, gender, disease stage, and parkinsonian medication dose. Also, information on training results, motivation, perceived attention during training, time of day for each training session will be analyzed and provide more information as to why some participants improve, and others do not. Apart from measuring transfer to other cognitive tasks, the iPARK trial will also assess changes in psychological health and wellbeing. Finally, very few studies on cognitive training in persons with PD have performed any long term assessment, therefore the four-month assessment included in this study will provide knowledge on the long-term effect of training.

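### The expectation items are asked only after training and record perceived benefit, so neither their correlation with gain nor an arm difference on them can separate expectation from a true effect

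*Protocol article*

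**What the plan says.** The section on placebo effects due to expectations in the protocol article takes from a cited source the view that "the effectiveness of the intervention could be questioned if the perceived intervention benefit correlates with improvement in that particular task". It gives its own aim as "To be able to measure expectations in relation to training gain". The question put to participants is "whether the participant believes the intervention has led to an improvement in four different tests": Digit Symbol, Letter Memory, Matrices and n-back. On timing, the items "will be assessed before each test during posttest (both directly after training and after 16 weeks"). Table 2 agrees. Its row "Expectation of improvement in certain tasks" is marked at the post-test and the 16-week follow-up only, with nothing at baseline or during the intervention.

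The Discussion names a second use: "expectations of improvement will be measured before some post-tests to see if the two groups differ in that respect". The next sentence concludes that "the iPARK trial will be able to answer if it is the updating itself that is causing the improvement".

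Two facts about the training bear on this. Under Intervention, "Feedback concerning numbers of correct answers are provided after each item as well as after each training task". Letter Memory is the criterion task in every session, and the primary outcome is a letter running span with a similar procedure.

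**The concern.** An expectation is held before the experience it concerns. These items come after 30 sessions and ask about improvement that has already happened, so they measure perceived benefit. For Letter Memory, participants have watched their own scores on nearly the same task for weeks. If the training works and they notice, real gain causes perceived benefit. The correlation that the cited criterion treats as a warning then appears with no placebo effect present. The arm comparison in the Discussion has the same weakness, because arms that truly differ in gain should also differ in perceived benefit.

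At stake is the reading of a positive primary result. The trial wants to attribute improvement to the updating component, and one of the checks offered in support cannot tell a placebo effect from a noticed true effect.

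**Working it through.** **1. The plan's own figure.** From the section on power and sample size: 40 per arm, difference in gain 2.6, SD 1.94, two-sided 5%, stated power 0.9996.
- Standard error = 1.94 × √(2/40) = 0.434, and 2.6/0.434 = 5.99.
- Power = Φ(5.99 − 1.96) = 0.99997; with the noncentral t, 0.99996.

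This agrees with the stated figure to within 0.0004. The point does not rest on it, but the same effect, SD and sample size are used below.

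**2. The missing input.** The documents give no correlation between perceived and real gain. Call it ρ within arms. It is an assumption, shown from 0 to 0.7.

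**3. Chance of a significant correlation, closed form.** By Fisher z, power = Φ(atanh(r) × √(n − 3) − 1.96).
- n = 80, r = 0.3: 0.3095 × 8.775 = 2.716, power 0.775.
- n = 80, r = 0.4: 0.4236 × 8.775 = 3.718, power 0.961.
- n = 40, r = 0.3: 0.3095 × 6.083 = 1.883, power 0.469.
- n = 40, r = 0.4: 0.4236 × 6.083 = 2.577, power 0.731.

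**4. Pooling the arms raises the correlation when training works.** Let perceived benefit have unit SD within arms and depend on gain only through ρ. At ρ = 0.3:
- Arm difference in perceived benefit = 0.3 × 2.6/1.94 = 0.402 SD.
- Covariance = 0.3 × 1.94 + (2.6/2) × (0.402/2) = 0.582 + 0.261 = 0.843.
- SD of gain = √(1.94² + 1.3²) = 2.335; SD of perceived benefit = √(1 + 0.201²) = 1.020.
- Pooled r = 0.843/(2.335 × 1.020) = 0.354.

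The Fisher formula at r = 0.354 and n = 80 gives Φ(0.370 × 8.775 − 1.96) = 0.90.

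**5. Simulation.** 3,000 trials per row, 40 per arm, SD of gain 1.94, no placebo effect. 'Correlation' means positive with p < 0.05.

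| ρ | Effect 2.6: correlation, arms pooled | Effect 2.6: correlation, trained arm | Effect 2.6: arms differ on perceived benefit | Effect 0: correlation, trained arm |
|---|---|---|---|---|
| 0 | 2% | 2% | 5% | 2% |
| 0.2 | 56% | 23% | 20% | 24% |
| 0.3 | 90% | 47% | 41% | 48% |
| 0.5 | 100% | 92% | 85% | 92% |
| 0.7 | 100% | 100% | 99% | 100% |

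The pooled 90% at ρ = 0.3 matches step 4.

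**6. Reading.** The trained-arm column is nearly the same whether the true effect is 2.6 or 0. The within-arm correlation therefore carries no information on whether the training works. The arm difference does rise with a true effect, and that is why it cannot be taken as a sign of a placebo effect.

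**The case against.** The strongest reply is that nothing hangs formally on these items. The criterion is attributed to a cited source in conditional terms, and the protocol itself says only that it wants to measure expectation in relation to gain. The Data analysis section sets no correlation test, threshold or veto. Efficacy is judged by the treatment-by-session term in the mixed model, and expectation is listed among the other pre-specified outcomes. All of this stands. A reader might infer that a working training would be declared ineffective, or that the primary test is compromised; the documents support neither.

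The attribution to updating also does not rest on these items alone. The Discussion puts the active control, blinding and equal presentation of the arms first. That stands too, but the concluding sentence follows directly on the expectation check, so that check is offered as part of the support.

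Direct score feedback concerns the trained tasks. Of the four tests asked about, only Letter Memory is among them, so the mechanism is established for one item in four. That one is the primary outcome.

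There is a reason to ask after exposure. Beliefs can diverge between arms once participants meet an easy fixed program or a harder adaptive one, and a pre-training item cannot register this. The reason is sound, but it does not turn a question about past improvement into a measure of expectation.

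The unseen statistical plan may say more about analysis. It cannot recover a prior expectation that was never collected.

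**Conclusion.** The point holds as one of measurement and interpretation. The items measure perceived benefit. For Letter Memory, a noticed real gain is enough to produce both the correlation and the arm difference, so neither can separate expectation from efficacy.

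The size depends on ρ, which is assumed. For ρ from 0.3 to 0.5, with the planned effect and no placebo component, a significant correlation appears in 90 to 100% of trials pooled and 47 to 92% in the trained arm, and the arms differ on perceived benefit in 41 to 85%. At ρ = 0 only chance findings remain. These are probabilities of a misleading pattern. They are not probabilities that the trial will be discredited, since no rule ties a conclusion to that pattern. The primary mixed-model test is unaffected.

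**What to change.** - Relabel the post-test items as perceived benefit and report them by arm.
- State that neither their correlation with gain nor an arm difference on them counts as evidence against efficacy or as evidence of a placebo effect. Do not rest the Discussion's attribution to updating on them.
- For participants still to be enrolled, ask the four items in prospective wording before training starts, after the standard instructions. Use them as a predictor or covariate of gain. Do not compare the arms on them: with randomisation, blinding and identical instructions, the arms can differ only by chance.
- If expectation by arm is wanted, repeat the prospective items after the first training session, alongside the motivation and focus questions that the program already asks.

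The wording changes cost almost nothing and apply to everyone, including those already enrolled. The new items are four short questions at an existing visit. Participants already enrolled will lack them, so any analysis of prior expectation covers a later subset only. An item asked after the first session is still only partly free of experienced performance.
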